### Interim analyses {21b}

There will be no interim analyses.

### Methods for additional analyses (e.g., subgroup analyses) {20b}

#### Retention to intervention at 12 months

Analysis of retention to the tapered dose will be performed with a paired analysis within the allocated group. Changes in percent from the time point for follow-up after the received intervention at 4 months (intervention) or 8 months (control) will be calculated. The analysis will be performed with repeated measures ANOVA.

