### Objectives {7}

Primary objective: To determine if tapering of medically prescribed opioids in a long-term non-cancer pain population is superior to control in reducing dispensed opioids and non-inferior regarding participants’ report on pain, pain cognitions, physical and mental health, quality of life, and functioning.

Secondary objective: To determine if a reduction in opioid intake displays stability over time.

Research hypothesis: Tapering of opioids in a structured intervention will reduce opioid intake by at least 50% and is superior to controls in reducing dispensed opioids.

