### Trial design {8}

The design of the present study is an RCT, which is under recruitment and conducted among patients with long-term pain who have been accepted to undergo a structured intervention aiming to taper opioid long-term treatments. The study population will be randomly allocated to either (1) the start of tapering opioids immediately or (2) the control group who will return to usual care and commence tapering of opioids 4 months later. A 12-month follow-up after the start of the intervention is included (Fig. 1). The study lies within a superiority framework. Primary endpoints are hypothesized to generate a decrease in opioid use in comparison to controls.

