### Participant timeline {13}

Participants will be enrolled in the trial for 12 months (intervention) or 16 months (control) following baseline assessment. The structured tapering intervention has a 4-month duration, but may be prolonged.

Participants denying tapering, but accepting to participate, will be followed up after 12 months for dropout analysis (Fig. 1).

A SPIRIT diagram (Table 1) is provided detailing the timing of enrolment, interventions, and assessments. Any methodological changes in the study design or sample size that may potentially affect the participants’ safety or study procedures will be discussed in the committee of ethics.

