### Sample size {14}

A “responder” to treatment is a participant who experiences at least a 50% reduction in opioid consumption [28]. Estimation of sample size was based on an effect size of 0.5 (Cohen’s *d*) 80% power, *α* = 0.05, and drop-off at 10%. The results from the calculation indicated the need for 70 individuals in each group.

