## Assignment of interventions: allocation

### Sequence generation {16a}

The allocation sequence is generated by computer to intervention or control in ratio 1:1 and is thereafter kept in sealed envelopes prepared by independent staff for an allocated group of 140 participants. Sealed envelopes will be kept in Lund and allocation will consequently take place in Lund.

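### The stability objective is analysed arm by arm although both arms receive the same taper and follow-up, so no overall estimate is given and each estimate uses about half the tapered participants

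*Protocol article*

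**What the plan says.** Under Objectives {7} the protocol article lists a single secondary objective: "Secondary objective: To determine if a reduction in opioid intake displays stability over time".

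The only analysis given for it is in Methods for additional analyses {20b}, under Retention to intervention at 12 months: "Analysis of retention to the tapered dose will be performed with a paired analysis within the allocated group". The quantity is then named: "Changes in percent from the time point for follow-up after the received intervention at 4 months (intervention) or 8 months (control) will be calculated". The method follows: "The analysis will be performed with repeated measures ANOVA". That section mentions no factor for arm and no estimate across arms.

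Both arms taper. Trial design {8} describes "the control group who will return to usual care and commence tapering of opioids 4 months later". On duration, Participant timeline {13} says: "Participants will be enrolled in the trial for 12 months (intervention) or 16 months (control) following baseline assessment". Plans for assessment {18a} sets the last questionnaire for all participants at 12 months after the start of tapering.

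**The concern.** Stability after tapering is a within-person question. Once controls have tapered there is no untreated comparator, and allocation determines only when a participant tapered, not what was received. A separate analysis in each arm therefore answers one question twice, each time with about half of the relevant participants, and gives no single estimate that addresses the objective.

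What is at stake is precision. An upward drift in dose after the taper is what this objective is meant to reveal. With a wider interval in each arm, a modest drift is harder to tell from none.

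**Working it through.** **1. Is the post-taper interval the same in both arms?**
- Intervention: tapering starts at month 0, the end-of-taper visit is at month 4, and enrolment ends at month 12. Interval: 12 − 4 = 8 months.
- Control: tapering starts at month 4, the end-of-taper visit is at month 8, and enrolment ends at month 16. Interval: 16 − 8 = 8 months.

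Measured from each participant's own start of tapering, both run from month 4 to month 12. The programme is the same, so pooling combines like with like.

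**2. Reproducing the planned sample size.** Sample size {14} states: "Estimation of sample size was based on an effect size of 0.5 (Cohen’s *d*) 80% power, *α* = 0.05, and drop-off at 10" per cent. Sequence generation {16a} gives the ratio: "The allocation sequence is generated by computer to intervention or control in ratio 1:1". Taking α as two-sided (the article does not say):

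n per group = 2 × (1.960 + 0.842)² / 0.5² = 62.8, rounded up to 63; 63 / 0.90 = 70.

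This matches the stated 70 per group. It also supplies the assumption used below: 63 completers per arm, 126 in all.

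**3. Precision of the within-person change.** The article gives no SD for the percent change, so results are in units of that SD, assumed equal in the two arms.

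95% CI half-width = 1.96 / √n:
- one arm: 1.96 / √63 = 0.247 SD
- all tapered: 1.96 / √126 = 0.175 SD
- ratio: √(126 / 63) = √2 = 1.41

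The change detectable with 80% power comes from a two-sided paired t-test at 0.05, used as a stand-in for the planned repeated measures ANOVA.

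| Quantity | One arm, n = 63 | All tapered, n = 126 |
|---|---|---|
| 95% CI half-width | 0.247 SD | 0.175 SD |
| Change detectable with 80% power | 0.36 SD | 0.25 SD |
| Power if the true change is 0.25 SD | 50% | 80% |

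**4. Sensitivity to losses during the wait.** If only 45 to 56 controls complete (an assumed range), the detectable change in the control arm alone is 0.43 to 0.38 SD. At the low end the control half-width is 1.96 / √45 = 0.292 SD, against 1.96 / √(63 + 45) = 0.189 SD pooled. The gain over the smaller arm then exceeds 1.41.

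**The case against.** **The wording may not mean two analyses.** The retention section follows one on differences between groups, so the phrase about the allocated group might only mean within-person rather than between-arm, and a repeated measures ANOVA can carry arm as a factor. This stands as a possibility. But no such factor is stated, and the separate month-4 and month-8 anchors sit more naturally with an arm-by-arm analysis. If a joint model is intended, one sentence settles it.

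**Arm-wise results are legitimate.** This stands. Controls spend 4 months in usual care first, and the per-protocol definition in {20a} requires them to attend a second baseline visit, so they may be a more selected group. That is a reason to display the arms, not to omit an overall estimate.

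**Time is already aligned.** This also stands. The abstract and the retention section both anchor to the start or end of each participant's taper. Only the pooling is new.

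**A stronger reading is tempting.** A reader might infer that the plan runs two tests of one objective, each at 0.05, that contradict each other up to half the time. With equal true drift and 63 per arm, one arm is significant and the other not with probability 2p(1 − p): 0.50 when power p is 0.50, and 0.32 when p is 0.80. With no drift, at least one arm is significant with probability 1 − 0.95² = 0.0975. The documents do not support that charge:
- The retention section sets no significance level; α appears only in the sample size.
- It sits under additional analyses, where no error control is promised.
- Stability is not defined by a p-value, and {20a} says continuous data come with 95% confidence intervals.
- One significant and one non-significant result do not contradict each other. With equal true drift, the two arm estimates differ significantly from each other only 5% of the time.
- A rule for reading a split result is detail that may sit in an analysis plan not shown here.

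Nor can each arm be called underpowered: the article gives neither a target drift nor an SD.

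**Conclusion.** The point holds as one of precision and clarity for the secondary objective. On the plain reading, the plan divides by arm a question that does not concern allocation, and states no overall estimate. Pooling would cut the 95% half-width from 0.247 to 0.175 SD and the change detectable with 80% power from 0.36 to 0.25 SD.

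These figures assume 63 completers per arm, equal SDs, a two-sided 0.05 level and a paired t approximation. The ratio of 1.41 depends only on equal arm sizes and equal SDs.

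The 4-month between-arm comparison is untouched. It would be wrong to read this as an error in the primary result, an inflated error rate or a built-in contradiction.

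**What to change.** In {20b}, keep the existing anchors (each participant's end-of-taper visit, and 12 months after that participant's start of tapering) and replace the arm-by-arm wording with something like:

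*The within-participant change will be estimated in one repeated measures analysis of all participants who received tapering, with allocated arm as a between-participant factor. The pooled change with its 95% confidence interval addresses the secondary objective. Arm-specific changes and the arm-by-time term will be shown descriptively.*

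The cost is a short change of text, with the same data and no extra collection. The article says register data are collected only after all follow-ups close, so as planned the change could be fixed before those data are seen.

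The downside is that the pooled figure averages over any effect of the 4-month wait, or of selection during it; the descriptive arm results show whether that matters.

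Pooling leaves two problems that need their own remedy. Percent change is undefined for anyone whose end-of-taper dose is zero. And under Primary outcomes in {12}, the dose covers the preceding 30 days at 4 months but the preceding 90 days at 12 months, so the two ends of the comparison are measured over different windows.

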### Intervention description {11a}

After randomization and at the baseline visit, a written individual treatment plan is established by the physician and reviewed by the nurse and participant in concordance with guidelines [27, 30].

The written treatment plan includes the following:
Information on well-known risks and side effects of long-term opioid treatments of long-term pain.Possible symptoms of withdrawal that might appear during tapering.The participant’s daily intake of opioid converted to milligram morphine equivalent dose per day (MME).The participants’ individual goals with tapering opioids.Information about follow-up: weekly follow-up at the commencement of tapering. Nurses’ follow-up is then performed according to participants’ needs which can be weekly or less frequent.The architecture of the tapering process where the participant is advised to decrease the dosage with approximately 5–10% from starting dose every week.The rationale for switching to a single preparation of extended-release opioid preparation if immediate-release opioids are used. If more than one type of opioid is used, tapering is performed with one drug at the time. If the patient is willing to taper pregabalin or benzodiazepines, this may be performed as well.Participant’s approval to prescribing doctor during the trial to use the Swedish drug register of the National Board of Health and Welfare. Opioids are prescribed with 7–30-day intervals or may be delivered by multi-dose dispensing by staff in intervals of 1 or 2 weeks if there are problems in following prescriptions.Information about urine drug screening and blood test for B-PEth that may occur at any time during the trial and should be performed on demand within 48 h. Refusal to perform the test is equal to a positive test. Results on drug screening are delivered approximately 1 week after sampling and are sent by post. If drug screening at baseline is without remark, no more drug screening is performed during tapering.Consequences that may occur if the treatment plan is not followed.The collaborative decision physician–participant on however evidence-based and safe pharmacological treatments for long-term pain, i.e., serotonin–norepinephrine reuptake inhibitor (SNRI), amitriptyline, and gabapentin, is in question to be tested after or during tapering.During tapering, rescue medication may be used. NSAID used for increased pain is and alimemazine, mirtazapine, or equal drug is in question to use for sleeping disturbance.Named contact nurse during the trial.

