#### Primary outcomes

Consumption of opioids, measured as MME, will be evaluated using data extracted from the Swedish drug register of the National Board of Health and Welfare (SDPR) where registration of all withdrawals of prescribed drugs is made. MME will be calculated using these data. At all baseline visits and 12-month follow-ups, the MME will be calculated for the preceding 90 days, but at 4 months after the intervention, the dose will be calculated for the preceding 30 days as the intervention is estimated to last approximately 3 months.

Self-reported opioid consumption will also be evaluated and reported in MME. Calculation of morphine equivalent dose will be performed with conversion factors used in Cochrane review [7].

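### Retention is set as percent change from the post-taper time point, a scale that is undefined at zero dose and unstable near zero, and the text leaves open whether the ANOVA uses it

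*Protocol article*

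**What the plan says.** The secondary objective (Objectives {7}) is "To determine if a reduction in opioid intake displays stability over time". The only analysis described for it is in Methods for additional analyses {20b}, under Retention to intervention at 12 months, in three sentences:

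- The first calls for a paired comparison inside each randomised arm.
- The second gives the measure and its reference point in each arm: "Changes in percent from the time point for follow-up after the received intervention at 4 months (intervention) or 8 months (control) will be calculated".
- The third names the model without saying which variable goes into it: "The analysis will be performed with repeated measures ANOVA".

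Four other places bear on the value that this scale divides by:

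- Intervention description {11a} advises participants to "decrease the dosage with approximately 5–10% from starting dose every week".
- Participant timeline {13}: "The structured tapering intervention has a 4-month duration, but may be prolonged".
- Primary outcomes, under Outcomes {12}: "at 4 months after the intervention, the dose will be calculated for the preceding 30 days". The reason given is that the intervention is expected to take about 3 months. For the other time points: "At all baseline visits and 12-month follow-ups, the MME will be calculated for the preceding 90 days".
- Follow-up visit at 4 months treats opioid intake that remains at that visit as a conditional case, so having none left is a foreseen result.

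No rule for a zero dose is given. The missing-data section {20c} covers questionnaire items only.

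**The concern.** The retention sentence names both a scale (percent) and a reference point (the follow-up after the taper). If the reference value is the dose at that point, the scale breaks down for the people who tapered furthest. Someone who reached zero has no percent change, either for sustained cessation or for relapse. Someone left on a very small dose can produce a huge percentage from a modest increase, and an ANOVA on means is sensitive to such values.

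At stake is the answer to the secondary objective. Whether reductions last is most informative in those with the largest reductions, and on this scale their data are either undefined or dominant. The problem would come from the scale alone, because the register supplies MME even for participants who discontinue or deviate (Plans to promote participant retention {18b}).

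**Working it through.** **Plan's own figure.** The retention analysis has no stated figure to reproduce. The only design figure is 70 per group (Sample size {14}: d = 0.5, 80% power, alpha 0.05, 10% drop-off; two-sided alpha assumed). n = 2 × (1.960 + 0.842)² / 0.5² = 62.8, so 63 evaluable per arm, and 63 / 0.90 = 70. It reproduces. The 63 is used below only for illustration.

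**Step 1: behaviour of the scale.** Percent change = 100 × (dose at 12 months − post-taper dose) / post-taper dose. The doses below are illustrative, with an assumed baseline of 100 MME.

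| Post-taper → 12 months (MME) | Change (MME) | Percent of baseline, change in points | Percent change from post-taper dose |
|---|---|---|---|
| 0 → 0 | 0 | 0 | undefined |
| 0 → 60 | +60 | +60 | undefined |
| 5 → 40 | +35 | +35 | 35/5 = +700% |
| 60 → 95 | +35 | +35 | 35/60 = +58% |
| 50 → 60 | +10 | +10 | 10/50 = +20% |

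**Step 2: can the post-taper dose be zero?** The advised reduction is a share of the starting dose, so the taper is linear and ends after 1/r weeks: 20 weeks at 5%, 10 weeks at 10%. The 4-month dose is a mean over the last 30 days. For it to be exactly zero, the taper must have ended before that window opens:

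- 4 months as 120 days, window opening at day 90: r = 1/(90/7) = 7.8% per week.
- 4 months as 122 days, window opening at day 92: r = 1/(92/7) = 7.6% per week.

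The part of the 5–10% range at or above these paces is (10 − 7.8)/5 = 44% to (10 − 7.6)/5 = 48%. This is a share of the range of paces, not of participants.

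With weekly steps, the first on day 0, over 122 days, the mean dose in the last 30 days is:

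| Weekly reduction | Weeks to zero | 30-day mean, % of starting dose |
|---|---|---|
| 5% | 20.0 | 21 |
| 6% | 16.7 | 6.5 |
| 7% | 14.3 | 0.4 |
| 7.5% | 13.3 | 0 |
| 10% | 10.0 | 0 |

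Stepwise reductions reach zero slightly sooner than a smooth line, so 7.5% already gives zero here. Paces of roughly 6 to 7.5% give small denominators instead.

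**Step 3: possible size.** The documents do not give the share at zero. If it were 10% to 50% of 63 per arm, 6 to 32 people would have no percent change and 57 to 31 would have one.

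An illustration under stated assumptions: 25 of 63 (40%) are at zero post-taper, 8 of them return to 60 MME, and the other 38 stay at 50 MME.

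- Mean MME post-taper = 38 × 50 / 63 = 30.2.
- Mean MME at 12 months = (38 × 50 + 8 × 60) / 63 = 37.8, a rise of 7.6.
- Mean percent change among the 38 for whom it exists = 0%.

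If percent change were the analysed variable, with no rule for zeros, the relapse would not show in it.

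**The case against.** Much can be said for the plan.

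- **The ANOVA may not use percent change.** One percent change per person is a single number, whereas a paired analysis and a repeated measures ANOVA need a value at each time point. The Abstract supplies these: mean daily MME at baseline, 4 and 12 months. The ANOVA could be on MME with percent change as description only, and then nobody is lost and a move from 0 to 60 MME counts in full. This stands as a possible reading, but the three sentences do not say so.
- **The denominator is inferred.** The sentence refers to a time point, not to the dose at it, and could mean a change in percent of baseline. This also stands, though the post-taper point is the only reference named.
- **Zero may be uncommon.** The research hypothesis is a reduction of at least 50%, not cessation. The pace is approximate, several opioids are tapered one at a time, nurses may slow the taper, and it may be prolonged. The number affected is therefore unknown.
- **A rule for zeros may sit in a fuller document.** Agreed, and its absence is not the point. The point is the scale and reference that the article does state.

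Two stronger inferences are tempting. A reader might conclude that those who reached zero are dropped, so that the analysis uses only people who did not finish the taper and cannot see relapse. The article states no exclusion, and means of MME reported under Statistical methods {20a} could still show a rise. A reader might also note that any pace of 1/(120/7) = 5.8% per week or faster reaches zero by day 120, which is most of the range. That is the dose on one day, whereas the outcome is a 30-day mean.

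**Conclusion.** The point holds in limited form. On the plain reading, the stated retention measure is undefined for any participant with 0 MME in the post-taper window and unstable for those close to it. The protocol's own pace and window make both foreseeable: exactly zero at about 7.6 to 7.8% per week or faster, near zero at roughly 6 to 7.5%. This assumes that the linear pace is kept and that the controls' 8-month dose uses the same 30-day window.

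The documents do not give the number of participants affected, do not say that they are excluded, and do not settle which variable enters the ANOVA. The size of any bias is therefore an assumption. The wording still needs correcting under every intention considered, because it is the only analysis described for the secondary objective.

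The post-taper dose covers 30 days and the 12-month dose 90 days. That is a separate comparability issue, which would remain on any scale.

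**What to change.** In the retention paragraph, state that:

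1. The analysed variable is MME, or dose as percent of the pre-taper baseline dose, at the post-taper and 12-month time points. For controls, say which baseline is meant; the second baseline visit immediately precedes their taper. The pre-taper dose should be positive, since eligibility requires more than 3 months of prescribed opioid use.
2. Zeros are included as values, for everyone who started the taper and has register data.
3. The proportion still at least 50% below baseline at 12 months is reported, which applies the protocol's own responder threshold.
4. Percent change from the post-taper dose is dropped as an analysed variable.

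A mixed model would be a reasonable choice but is optional, because the change of scale solves the problem by itself. Add a line noting the 30-day versus 90-day windows as a comparability limit.

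The cost is a few sentences and no new data. Register data are extracted only after all follow-ups close, so the change can be fixed before they are seen.

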**Methods:**

The study is a randomized controlled trial. The sample size was set to a total of 140 individuals after estimation of power and dropout. Participants will be recruited from a population with long-term non-malignant pain who will be randomly allocated to (1) the start of tapering immediately or (2) the control group who return to usual care and will commence tapering of opioids 4 months later. A 12-month follow-up is included.

When all follow-ups are closed, data from the Swedish drug register of the National Board of Health and Welfare will be collected and individual mean daily opioid dose in morphine equivalents will be calculated at three time points: baseline, 4 months, and 12 months after the start of the intervention. At the same time points, participants fill out the following questionnaires: Numeric Pain Rating Scale (NPRS), Tampa Scale of Kinesiophobia (TSK), Pain Catastrophizing Scale (PCS), Chronic Pain Acceptance Questionnaire (CPAQ-8), Hospital Anxiety and Depression Scale (HADS), and RAND-36. At baseline and follow-up, a clinical assessment of opioid use disorder is performed.

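### The retention analysis measures change only from the post-taper dose in all analysed participants, so on its own it does not answer whether a reduction is stable

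*Protocol article*

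**What the plan says.** The protocol article, Objectives {7}, sets the aim: "To determine if a reduction in opioid intake displays stability over time".

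The analysis for it is in Methods for additional analyses {20b}, under Retention to intervention at 12 months, and has three parts:

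- the comparison: "Analysis of retention to the tapered dose will be performed with a paired analysis within the allocated group";
- the measure: "Changes in percent from the time point for follow-up after the received intervention at 4 months (intervention) or 8 months (control) will be calculated";
- the method: "The analysis will be performed with repeated measures ANOVA".

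Two elements that could link this analysis to the objective appear elsewhere but are not used here. Sample size {14} defines a responder: this "is a participant who experiences at least a 50% reduction in opioid consumption". The abstract, counting from taper start, says that "individual mean daily opioid dose in morphine equivalents will be calculated at three time points: baseline, 4 months, and 12 months". Outcomes {12} adds that register MME covers the preceding 90 days at all baseline visits and at 12 months, and the preceding 30 days at the 4-month visit.

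**The concern.** Before a reduction can be stable, there must be a reduction. A percentage anchored to the post-taper dose asks only whether the dose moved afterwards. Someone who never reduced has nothing to lose and scores 0%, the same as someone who tapered and held.

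The within-group figure therefore mixes two things: relapse among people who tapered, and unchanged dosing among people who did not. The more of the second kind the analysed set contains, the closer the average is to no change. A reader of the 12-month result could take a diluted figure as evidence of durability, and could not tell from it whether participants were back near their pre-taper dose.

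**Working it through.** **The plan's own figure.** The only computed figure in the article is 70 per group. With d = 0.5, 80% power and two-sided α = 0.05 (sidedness assumed), n = 2 × (1.960 + 0.842)² / 0.5² = 62.8, rounded up to 63. Then 63 / 0.9 = 70. It reproduces, and nothing below depends on it.

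**Notation.** D0 is the pre-taper dose, D1 the post-taper dose (4 months intervention, 8 months control) and D2 the dose 12 months after taper start.

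- Plan's measure: R = 100 × (D2 − D1) / D1.
- Reduction still present at 12 months: P = 100 × (D0 − D2) / D0.

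**Single participants** (doses in MME, assumed for illustration):

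| Pattern | D0 / D1 / D2 | R | P | At least 50% below D0 at D1 and D2 |
|---|---|---|---|---|
| Never reduced | 100 / 100 / 100 | 0% | 0% | no |
| Reduced 10%, held | 100 / 90 / 90 | 0% | 10% | no |
| Halved, held | 100 / 50 / 50 | 0% | 50% | yes |
| Large taper, small regain | 100 / 20 / 30 | +50% | 70% | yes |
| Large taper, half of it lost | 100 / 25 / 62.5 | +150% | 37.5% | no |

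The first three rows are identical on R, although only the third is a stable reduction by the protocol's responder definition. The fourth scores worse than the first while keeping a 70% reduction.

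**Mixed groups.** Let a share s be responders and let the rest stay at exactly 100 (assumed).

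- Case A: responders go 100 / 25 / 62.5. Mean individual R = 150s. With group means, D1 = 100 − 75s and D2 = 100 − 37.5s.
- Case B: responders go 100 / 20 / 30. Mean individual R = 50s and mean P = 70s.

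| s | A: mean of individual R | A: change in group means | B: mean of individual R | B: mean P |
|---|---|---|---|---|
| 0 | 0% | 100 to 100, 0% | 0% | 0% |
| 0.25 | +37.5% | 81.25 to 90.625, +11.5% | +12.5% | 17.5% |
| 0.5 | +75% | 62.5 to 81.25, +30% | +25% | 35% |
| 0.75 | +112.5% | 43.75 to 71.875, +64.3% | +37.5% | 52.5% |
| 1 | +150% | 25 to 62.5, +150% | +50% | 70% |

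In case A the relapse per responder is the same in every row, but the reported figure changes with s. In case B the group that looks most stable (s = 0) is the one with no reduction at all.

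**Do low reducers stay in the analysed set?** Some do.

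- Intervention description {11a} lets the nurse slow the taper.
- The 4-month visit provides for participants still taking opioids.
- {11b} allows a non-compliant participant to be kept after the plan is renewed.
- The per-protocol set in {20a}, stated for the 4-month comparison, rests on attendance, not on dose.

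**Does another stated analysis fill the gap?** {20a} compares the arms at 4 months. It covers the intervention arm's taper but not month 12, and not the controls' change from their second baseline to 8 months. No stated test sets the 12-month dose against the pre-taper dose.

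**The case against.** The other side has five fair points.

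1. *Baseline may be in the model.* With two time points, repeated measures ANOVA is equivalent to a paired t-test, which {20a} names separately, and the abstract lists three time points. Including baseline is a natural reading, so a reader should not infer that the pre-taper dose is excluded. This stands: the time points are simply not stated. It does not remove the problem. The percentage is still tied to the post-taper visit, and whole-group means cannot separate the two kinds of participant. In case A at s = 0.5 the means run 100, 62.5, 81.25, exactly as they would if every participant followed that path.
2. *Not everyone is analysed.* {11b} drops persistent non-adherers from the final analysis, and {13} keeps those who decline tapering for a dropout analysis only. This stands, and it removes some of the flat doses. Attenders with a slowed or small taper remain.
3. *A failed taper would be seen.* One might infer that it would pass as a stable success. The documents do not support that for the intervention arm, because the 4-month comparison would show it. The remaining gap is the controls' own taper.
4. *Pre-taper and 12-month MME are both computed.* They could be set side by side descriptively. That is true, so the lack is of a stated formal comparison, not of data.
5. *The illustration is chosen.* Non-responders need not stay flat, since further tapering support is offered after month 4, and the plan does not say that individual percentages are averaged. This also stands.

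It can be added that responder strata and denominators belong in a full analysis plan. The reference point, however, is stated in the article, and it does not match the objective.

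**Conclusion.** The point holds in limited form. The stated measure refers only to the post-taper dose, in all analysed participants. Those who reduced little or not at all count as having held their dose and dilute relapse among those who tapered. This measure alone therefore does not answer the secondary objective.

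The size cannot be fixed from the documents. Under the assumed doses with half responders, a +150% relapse appears as +75% or +30%, depending on how percentages are averaged. The full span from 0% to +150% needs responder shares from none to all and exactly flat non-responders, so it illustrates the direction and is not a forecast.

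The primary comparison at 4 months is unaffected. The change should still be made, because this is the only analysis stated for the secondary objective.

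**What to change.** In {20b}:

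1. State the time points of the repeated measures analysis and include pre-taper register MME: the baseline visit for the intervention arm, the second baseline visit for controls.
2. As the main stability measure, report in all allocated participants the proportion at least 50% below pre-taper MME at both the post-taper visit and 12 months after taper start, with a 95% CI. Add the 12-month change from pre-taper MME.
3. As descriptive only, report the proportion of post-taper responders still at least 50% below at 12 months, and the percent change from the post-taper dose split by response. Note that these condition on response, that the responder proportion has a smaller denominator, and that a 30-day post-taper window is set against a 90-day window at 12 months. With opioids prescribed at 7–30-day intervals, a dispensing gap could create an apparent responder who then seems to relapse.

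Two counting rules should be written down with measure 2: how controls without a second baseline visit are counted, and how participants on opioid replacement therapy are counted. The article says that such therapy is absent from the register and is taken from medical records at 12 months, so register MME alone could score these participants as reduced.

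The cost is wording. Register MME is already planned at these visits, and {18b} retrieves it for those who discontinue or deviate. The register data are extracted only after all follow-ups close ({18a}), so the definitions can be fixed before those data are seen. A pre-taper denominator also avoids the division by zero that R meets when a participant has tapered fully.
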